#### Interim analyses {21b}

Although there are no anticipated problems that may be detrimental to the participants, serious life-threatening AEs leading to prolonged hospital stay or death will be reported to the Institutional Review Board (IRB), and our study will be terminated immediately.

#### Methods for additional analyses (e.g., subgroup analyses) {20b}

Prior to statistical analysis, a sub-investigator will review the data record forms to check for their legitimacy and identify the missing data. The subgroup analysis will be conducted to evaluate outcomes in patients based on their baseline clinical and demographic characteristics, such as gender, age, weight, and type of surgery (laminectomy or laminoplasty).

#### Methods in analysis to handle protocol non-adherence and any statistical methods to handle missing data {20c}

All researchers will be trained referring to the same training protocol. Protocol modifications will not be expected. Missing intraoperative data, if any, will be obtained from the electronic hospital files. Postoperative evaluation at specified time points is mandatory, and missing postoperative data are not to be anticipated. Analyses of all outcomes will be performed according to the intention-to-treat principle, and once enrolled, all participants will be analyzed, regardless of the findings.

#### Plans to give access to the full protocol, participant level-data, and statistical code {31c}

The data collected will be kept in a secure cabinet. Only the research members and the IRB of Beijing Tiantan Hospital will have access to the files. After the completion of the study, the results will be made public through publication in a scientific journal along with conferences related to neurosurgical anesthesia, as well as the ClinicalTrials.gov website. The data generated or analyzed during this study will be considered to be available from the corresponding author on reasonable request.

### Oversight and monitoring

#### Composition of the Coordinating Center and Trial Steering Committee {5d}

The Coordinating Center (CC) will comprise a Principal Investigator (PI), an expert on pain management, a neurosurgeon, a neurosurgical nurse, and a statistician. The CC will establish a communication network between the research members involved in the recruitment, preoperative evaluation, perioperative intervention, postoperative evaluation, and follow-up process. It will be responsible for the training of the research members regarding every aspect of the study protocol, along with the coordination of all standardized quality control aspects of the trial including the operations manual, forms, etc. The CC will also supervise data management, analysis, and publications of the study.

The Trial Steering Committee (TSC) will include the PI, an independent chair, two independent clinicians, an independent statistician, and representatives from the funding institution, who will oversee the work of various subcommittees. The subcommittee responsible for quality control will ensure standardized training for research members regarding the study protocol and their performance review. A subcommittee comprising the neurosurgical staff will oversee recruitment and clinical activities. Another subcommittee will oversee the review and approval of publications and presentations.

Participants will be recruited from the neurosurgical outpatient department at Beijing Tiantan Hospital, affiliated to Capital Medical University, Beijing, China. Based on the inclusion and exclusion criteria, patients will be screened for study participation by the subcommittee comprising the neurosurgical research members of the trial. Patients scheduled for surgery who fulfill the eligibility criteria and express an interest in participating in the study will be visited by a research assistant, 1 day before the surgery, to obtain written consent. A verbal explanation of the written consent will be provided by the research member, and any questions regarding the study will be answered. If the patients are willing to participate, written consent will be obtained, and patients will be taught how to indicate postoperative pain levels based on the VAS and how to use the PCA device when they feel pain.

The TSC will be responsible for overseeing the progress of the trial, for overall supervision, and for finding solutions to unforeseen problems that may arise in the course of the study.

The TSC will perform thorough assessment of the potential association between the study interventions and the AEs and will report to the IRB if necessary. The IRB of Beijing Tiantan Hospital will supervise the trial and will meet at least annually to oversee conduct and progress.

A Stakeholder and Public Involvement Group (SPIG) has not been appointed for this trial.

#### Composition of the Data Monitoring Committee, its role and reporting structure {21a}

An independent Data Monitoring Committee (DMC), responsible for independent review of participant safety and data endpoints, has been appointed. The independent members include two statisticians and a clinician. The DMC will report directly to the TSC at their meeting after every 25%, 50%, 75%, and 100% of patient inclusions.

#### Adverse event reporting and harms {22}

The IRB of Beijing Tiantan Hospital will conduct regular inspections of the trial progress. Any AEs will be recorded, and a thorough assessment of the potential association between the study interventions and the AE will be carried out. Serious life-threatening AEs leading to prolonged hospital stay or death will be reported to the IRB, and the PRE-EASE trial will be terminated immediately.

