### Criteria for discontinuing or modifying allocated interventions {11b}

A detailed recording of all adverse events (AEs) throughout the course of the study will be properly recorded, closely monitored, and reported to the ethics committee as soon as possible, with the intentions of a resolution or stabilization, or even termination of the study if necessary.

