## Discussion

This trial will be a PROBE study. It will have better application in routine clinical practice, along with the clinical outcomes of a large simple research, which will permit a broader patient population and will include the advantage of randomization and an extensive evaluation of endpoints by blinded experts [19]. To our knowledge, there has been no attempt in the past to infiltrate laminoplasty or laminectomy with a preemptive local administration of betamethasone and ropivacaine. This study will add significant new knowledge to the effect and feasibility of preemptive wound infiltration of betamethasone.

Due to its large particles occluding the blood vessels supplying the spinal cord, betamethasone was previously reported to result in infarction of spinal cord after epidural analgesia [20]. However, we speculate that local peri-incisional infiltration of betamethasone is safe, as betamethasone has previously been used for intralesional [21], local infiltration [22], intramuscular [23], and intra-articular injections [16]. Local infiltration of steroid hormones will undeniably present the risk of delayed wound healing or local infection. However, we intend to use the lowest possible concentration of betamethasone for local infiltration based on the previous literature [15, 16, 22, 24], and thus this concentration should be considered safe. Wound healing and infection will be closely observed. The study will be immediately terminated in case of serious adverse reactions by the PRE-EASE Trial Management Group.

There are still some limitations regarding our study. Firstly, this is a single-center study; a multicenter study would be helpful in providing more significant data. In addition to incisional pain, acute pain after laminoplasty or laminectomy may be followed by long-term chronic pain that may not only originate from the incisional wound, but may also include neuropathic pain from spinal cord damage and nerve root injury. Another possible limitation of this study is that it will only involve infiltration of the surrounding tissue of the incision site. Therefore, we would like to suggest a further detailed study, regarding whether local betamethasone injection into the affected nerve roots before closure could be beneficial for postoperative pain after laminoplasty or laminectomy.

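### The harms rule ends the trial at once for serious life-threatening events, whatever the arm or cause, and conflicts with the termination wording in two other sections

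*Protocol article*

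**What the plan says.** The protocol article deals with ending the trial for safety in four places.

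- **Adverse event reporting and harms {22}:** "Serious life-threatening AEs leading to prolonged hospital stay or death will be reported to the IRB, and the PRE-EASE trial will be terminated immediately". The sentence just before it provides that "a thorough assessment of the potential association between the study interventions and the AE will be carried out".
- **Interim analyses {21b}:** the same kind of event is reported to the review board, "and our study will be terminated immediately".
- **Criteria for discontinuing or modifying allocated interventions {11b}:** all adverse events are recorded and reported to the ethics committee with a view to resolution, "or even termination of the study if necessary".
- **Discussion:** "The study will be immediately terminated in case of serious adverse reactions by the PRE-EASE Trial Management Group".

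Two other sections set up the safety review. Under {5d}, "The TSC will perform thorough assessment of the potential association between the study interventions and the AEs". Under {21a}, an independent DMC is "responsible for independent review of participant safety and data endpoints", and "The DMC will report directly to the TSC at their meeting after every 25%, 50%, 75%, and 100% of patient inclusions".

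**The concern.** A rule that ends the whole trial has to be unambiguous before the first serious event. Here {22} and {21b} order termination with no qualification, {11b} leaves it to judgement, and the Discussion changes both the trigger and the actor. A reader cannot tell which applies.

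The unconditional version also leaves the causality assessment and the DMC without a stated part in the most serious safety decision. A complication of the surgery itself, in a patient who never received betamethasone, would satisfy its wording. The trial could then lose part of its primary answer for a reason unrelated to the treatment. Otherwise someone would have to choose between the sections after the event, in an open-label trial.

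**Working it through.** **1. The wording side by side**

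| Section | Trigger | Automatic? | Who decides | Tied to causality or DMC review? |
|---|---|---|---|---|
| {22} | Serious life-threatening event with prolonged stay or death | Yes | Not stated | No; assessment is in the preceding sentence but its result is not used |
| {21b} | Same | Yes | Not stated | No |
| {11b} | Any adverse event | No, only where needed | Not stated | No |
| Discussion | Serious adverse reaction | Yes | Trial Management Group | Only if reaction is read in its usual sense of a related event |

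The Trial Management Group is not among the bodies described under {5d} and {21a}, which are the Coordinating Center, the Trial Steering Committee and its subcommittees, the review board and the DMC. It appears again only under Data Availability.

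**2. A test case.** Take a postoperative death in the control arm, judged to be due to the surgery. Sections {22} and {21b} terminate the trial. Section {11b} asks whether termination is needed. The Discussion rule is not triggered, if a reaction means a related event. The sections give three different answers. Outcomes {12} itself lists serious adverse effects and death among complications that may affect follow-up, so such events are foreseen.

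**3. How often the literal rule could be triggered.** Inputs: 116 patients, 58 per group, 1:1 allocation (Trial design {8}, Sample size {14}) and six months' follow-up. The event rate p is not in the documents and is assumed here. The chance of at least one event among N patients is 1 − (1 − p)^N.

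| Assumed p over 6 months | All 116 patients | The 58 controls alone |
|---|---|---|
| 0.1% | 1 − 0.999^116 = 11% | 6% |
| 0.5% | 1 − 0.995^116 = 44% | 25% |
| 1% | 1 − 0.99^116 = 69% | 44% |
| 2% | 1 − 0.98^116 = 90% | 69% |

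The chance for all 116 passes one half at p = 1 − 0.5^(1/116), about 0.6%. The controls column applies the same rate to both arms, that is, no drug effect on these events.

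**4. What an early stop would cost the primary analysis.** First, the plan's own figure. Sample size {14} assumes 120 ± 90 mg against 70 ± 50 mg, two-sided α of 0.05, 90% power and 20% dropout. The difference is 50 and the common SD is √((90² + 50²)/2) = 72.8. The normal approximation gives (1.960 + 1.282)² × (90² + 50²)/50² = 44.6, so 45 per arm. With the t distribution it is 46 per arm, and 46/0.8 = 57.5, so 58 per arm and 116 in total. The stated size is reproduced.

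On the same assumptions, power is Φ(50/√(10,600/n) − 1.96), where n is the number analysed per arm:

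| Enrolled at stop | n per arm after 20% dropout | Power | Power with no dropout |
|---|---|---|---|
| 29 | 11.6 | 38% | 46% |
| 58 | 23.2 | 65% | 74% |
| 87 | 34.8 | 82% | 89% |
| 116 | 46.4 | 91% | 96% |

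The first three rows are the DMC's 25%, 50% and 75% points.

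**5. Linking steps 3 and 4.** The probabilities in step 3 run to the last patient's sixth month. They include events after enrolment has closed, and events after a patient's 48-hour butorphanol total is already recorded. They are therefore upper figures for the chance that the primary analysis is cut short.

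**The case against.** The best defence is that an immediate halt for the gravest events is a cautious choice in a protocol approved by the review board, and that it can coexist with scheduled DMC reviews. Section {11b} covers all adverse events while {22} and {21b} cover a severe subset, so general discretion beside a specific rule is partly compatible. The text speaks of events in the plural, and the Discussion is explanatory prose in a condensed article.

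Much of this stands. The DMC is given no exclusive power to stop the trial, so the automatic rule bypasses it without formally contradicting it. That a single event suffices is the literal reading, drawn from the absence of any count. What the defence does not remove is the difference in trigger and deciding body between {22} and the Discussion, or the absence of any link between the causality assessment and the termination sentence that follows it.

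Three stronger readings are tempting but not supported:

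- **That early termination is likely.** No event rate is given. The trigger is narrow, and the patients are ASA I or II, aged 18 to 64, with several higher-risk groups excluded. Below about 0.6% per patient, termination is less likely than not.
- **That a stopped trial would tell us nothing.** With 87 enrolled, power is still about 82% on the plan's assumptions, and an event late in follow-up could come after all the primary data are in.
- **That the four DMC reviews inflate the type I error.** The protocol gives the DMC a review of endpoint data but plans no interim efficacy test, and DMC operating details commonly sit in documents not shown here.

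**Conclusion.** The point holds as a fault in a stated rule. Sections {22} and {21b} end the trial without regard to cause, arm or number of events. They differ from {11b} on discretion and from the Discussion on trigger and deciding body, and they give the existing safety review no stated role. This rests on the text alone.

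The practical size is conditional. The 11% to 90% range follows from assumed rates of 0.1% to 2%, independent events and complete six-month follow-up of all 116 patients. The loss of power depends on when a stop occurs and on the plan's means, SDs and dropout. The supportable conclusion is that one unrelated event could end the trial, with a probability the documents do not fix.

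**What to change.** Reconcile {11b}, {21b}, {22}, {5d}, {21a} and the Discussion into one trial-level termination rule, stated once and cross-referenced elsewhere. It should:

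- state the trigger, including whether relatedness, arm and number of events matter;
- say how the causality assessment and the DMC review already provided for enter the decision, including for an event between scheduled reviews;
- name one deciding body, and either describe the Trial Management Group among the oversight bodies or remove it from this decision.

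Where the clinical threshold lies, and whether the halt stays automatic, is for the sponsor, the DMC and the review board. The cost is a wording amendment with ethics notification by the route in section {25}. The Trial Steering Committee and the DMC already exist, and neither the sample size nor data collection changes.

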#### Frequency and plans for auditing trial conduct {23}

The IRB of Beijing Tiantan Hospital will make regular inspections of the trial conduct. The inspections will be independent of those of the investigators and the sponsor.

#### Plans for communicating important protocol amendments to relevant parties (e.g., trial participants, ethical committees) {25}

Although protocol amendments are not to be expected, any deviations from the protocol will be fully documented in a breach report form, reported to all regulatory bodies, and thoroughly recorded in a protocol deviation log. Protocol amendments will be first submitted to the sponsor within 7 days and then to the relevant parties by sending the updated protocol to the investigators. A copy of the revised protocol will be added to the Investigator Site File. The protocol will also be updated in the ClinicalTrials.gov registry website.

#### Dissemination plans {31a}

After the completion of the study, the results will be made public through publication in a scientific journal, at conferences related to neurosurgical anesthesia, and on the ClinicalTrials.gov website.

## Discussion

This trial will be a PROBE study. It will have better application in routine clinical practice, along with the clinical outcomes of a large simple research, which will permit a broader patient population and will include the advantage of randomization and an extensive evaluation of endpoints by blinded experts [19]. To our knowledge, there has been no attempt in the past to infiltrate laminoplasty or laminectomy with a preemptive local administration of betamethasone and ropivacaine. This study will add significant new knowledge to the effect and feasibility of preemptive wound infiltration of betamethasone.

Due to its large particles occluding the blood vessels supplying the spinal cord, betamethasone was previously reported to result in infarction of spinal cord after epidural analgesia [20]. However, we speculate that local peri-incisional infiltration of betamethasone is safe, as betamethasone has previously been used for intralesional [21], local infiltration [22], intramuscular [23], and intra-articular injections [16]. Local infiltration of steroid hormones will undeniably present the risk of delayed wound healing or local infection. However, we intend to use the lowest possible concentration of betamethasone for local infiltration based on the previous literature [15, 16, 22, 24], and thus this concentration should be considered safe. Wound healing and infection will be closely observed. The study will be immediately terminated in case of serious adverse reactions by the PRE-EASE Trial Management Group.

There are still some limitations regarding our study. Firstly, this is a single-center study; a multicenter study would be helpful in providing more significant data. In addition to incisional pain, acute pain after laminoplasty or laminectomy may be followed by long-term chronic pain that may not only originate from the incisional wound, but may also include neuropathic pain from spinal cord damage and nerve root injury. Another possible limitation of this study is that it will only involve infiltration of the surrounding tissue of the incision site. Therefore, we would like to suggest a further detailed study, regarding whether local betamethasone injection into the affected nerve roots before closure could be beneficial for postoperative pain after laminoplasty or laminectomy.

### Trial status

This research protocol version 2 (2019/12/22) is approved by the IRB of Beijing Tiantan Hospital, affiliated to Capital Medical University. Recruitment of patients for this PRE-EASE trial will begin in February of 2020, and is expected to complete by the end of 2021.

## Data Availability

After the completion and following the publication of the PRE-EASE trial, requests for data sharing will be considered by the PRE-EASE Trial Management Group.

## Abbreviations

AE: Adverse event
GI bleeding: Gastrointestinal bleeding
IRB: Institutional Review Board
ODI: Oswestry Disability Index
PCA: Patient-controlled analgesia
PONV: Postoperative nausea and vomiting
POSAS: Patient and Observer Scar Assessment Scale
PSS: Patient Satisfaction Score
RSS: Ramsay Sedation Scale
VAS_M_: Visual Analog Score during movement
VAS_R_: Visual Analog Score during rest
WHOQOL-BREF: World Health Organization Quality of Life-BREF
